## Abstract

**Background:**

Psychological and study skill difficulties faced by students in higher education can lead to poor academic performance, sub-optimal mental health, reduced study satisfaction, and drop out from study. At the same time, higher education institutions’ support services are costly, oversubscribed, and struggle to meet demand whilst facing budget reductions. The purpose of the proposed study is to evaluate the acceptability of a new online intervention, MePlusMe, aimed at students in higher education facing mild to moderate psychological and/or study skill difficulties. The study will also assess the feasibility of proposed recruitment and outcome assessment protocols for a future trial of effectiveness. The system supports self-management strategies alongside ongoing monitoring facilitated by a messaging service, as well as featuring a built-in community of student users. It is based on current clinical guidelines for the management of common mental health problems, together with best practice from the educational field.

**Methods/design:**

Two hundred and forty two students will be recruited to a within-subjects, repeated measures study conducted over 8 weeks. Self-report measures of depression and anxiety symptoms, mental wellbeing, academic self-efficacy, and everyday functioning will be collected at baseline, and then at 2, 4, and 8 weeks. During this period, students will have access to the intervention system. UK higher education institutions Bournemouth University and University of Warwick will participate in the study. Data on student satisfaction and engagement will also be collected. Study findings will help to determine the most appropriate primary outcome and the required sample size for a future trial.

**Discussion:**

This study will evaluate the acceptability of an online intervention system for students facing psychological and/or study skill difficulties and will test recruitment procedures and outcome measures for a future trial of effectiveness. The system is designed to be implemented as a stand-alone service or a service complementary to student support services, which is accessible to the majority of students and effective in improving student experience at higher education institutions.

## Background

There is growing concern about the mental health and wellbeing of higher education (HE) students [1–4], not least because of associations with academic performance. Higher education institutions (HEIs) have an obligation to provide support for the mental health and wellbeing of their enrolled students. Demand for student support services (SSS) is increasing [5], which is likely to result in increased waiting times before students receive support. This may increase the risk of their problems escalating, and may lead to negative consequences for both the individual and HEIs. The proportion of HE students who fail to complete their studies has recently risen to more than 22 % in the UK [3]. Recent UK HEI fee increases [6, 7] add further pressure on HEIs to be cost-effective, show quality and value for money, and enhance ‘student experience’—an important influence on the ratings, intake, and income of HEIs.

**Fig. 1 Fig1:**
[figure not shown]
Overview of the study procedure

A number of reports have documented the mental health problems experienced by HE students [2–4, 8–10]. This literature indicates a high prevalence of mental health problems, although there is an absence of well-conducted studies in this area. Responses to a recent electronic survey conducted by the UK National Union of Students showed that 8 % of the students identified as ‘having a mental health problem but not seeking diagnosis’, 2 % identified as ‘currently seeking for a diagnosis’, and 10 % of students identified themselves as having been diagnosed with a mental health problem and believed this diagnosis still applied to them [10]. Alongside this, the Royal College of Psychiatrists [4] noted that 4 % of HE students in the UK seek help from a counsellor for emotional and psychological difficulties each year. Official statistics from HESA suggest that the proportion of students in the UK declaring a mental health difficulty on entry to university has gone up from 0.5 % between 1994 and 1995 to 3.6 % between 2006 and 2007, while numbers have doubled between 2012 and 2013 [6]. A much larger proportion experience psychological or study skill-related difficulties that keep them from achieving their true academic potential and enjoying the university experience to its fullest [4, 9]. This finding is supported by another UK study that found 90.5 % of students surveyed would rank exams or assessments as reasonably stressful or very stressful, while other stressors identified included time management and deadlines (83.3 %), and considering career prospects (75.2 %) [11].

Alongside these challenges, HEIs are facing major cuts to their budgets. In the last UK Governmental Spending Review, cuts of up to 40 % over 4 years were announced [12]. This further challenges the ability of UK HEIs to offer effective student support services. On-site SSS exist to deal with students’ psychological and study skill difficulties, yet limited resources mean that they struggle to cope with the high demand [4, 9]. In some cases, the average waiting time between referral and assessment for counselling is 9 weeks, i.e. more than one academic term [13]. Seeking help via private routes is an alternative option, but usually at a cost unlikely to be affordable for most students. A further concern is that the high demand reported is unlikely to mirror true needs. As many as 30 % of students would not feel comfortable to report their concerns [11], and consequently their needs remain unidentified and thus unmet.

Therefore, alternative means of supporting students should be sought, especially for students who experience mild to moderate difficulties that impact on their studies and student experience and whose needs are not prioritised within HEIs SSS. The Royal College of Psychiatrists [4] has proposed ‘to increase the availability of, and access to, self-help programs such as proprietary or web-based interactive cognitive-behavioural therapy (CBT)’ (p. 20). Online interventions are effective, easy-to-use, low-cost, and can be used anonymously without the potential stigma related to face-to-face treatment [14]. The internet is rapidly expanding as a support tool for psychological problems [15] and as a platform for the delivery of psychological therapies [16, 17]. Treatment of depression using internet-based CBT or problem-solving therapy (PST) has been found to be successful [18, 19], and potentially as effective as face-to-face therapy [19]. A recent systematic review indicated that for many mental health problems, there is little difference between different self-help approaches and whether or not there was guidance and administration by a practitioner [20]. Moreover, internet-based support systems can offer access to psychological and study skill support for a complete cohort of students across each HEI, overcoming the time and resource limitations to which traditional support services are subject.

However, there is limited literature regarding existing internet-based support systems specifically designed for HE students. The few online systems that are on offer to address psychological needs of adults, such as ‘MoodGym’ [21], ‘e-couch’ [22], and ‘Living Life to the Full’ [23], are designed for the general population. A system currently on offer by some HEI for the support of their students is Computer Aided Lifestyle Management (CALM), but there is very limited material describing its development or investigating its feasibility, effectiveness, or student satisfaction [24]. Another online psychological treatment is the ‘SilverCloud Health’ platform [25], which provides help and support packages. Current programmes available target symptoms of depression, stress, anxiety, and eating disorders. However, neither ‘SilverCloud’ nor ‘CALM’ address study skill problems. MePlusMe will fill this gap.

### MePlusMe

Recently, iConcipio has developed an online multimedia intervention called MePlusMe, which meets the need for a system addressing mild to moderate psychological and/or study skill difficulties of HE students. It is an easy-to-use system offering two different routes, a symptoms-route (‘Questionnaire’) or a techniques-route (‘Library’), to access support techniques that match differing styles and needs, ensuring maximum flexibility and utility of the system. Students can practice these techniques in their own time and space, as and when needed, whilst using a rating system to monitor their progress. This ongoing self-management aims to promote students’ personal effectiveness in addressing internal challenges and environmental demands. The self-monitoring process is further supported by a messaging service, in the form of motivational reminders to the user’s inbox within the system, to their personal email accounts, and, if they choose to, to their personal mobile phone. These messages encourage them to return to the system to practise the techniques and complete the post-intervention measures. Furthermore, a social network where students can post their thoughts on the ‘Thought Wall’ and other students have the option to ‘like’ or ‘share’ these thoughts in other social media (Facebook and Twitter) is present, allowing students to interact with each other anonymously for mutual support.^1^ This built-in community of students acts as an additional support resource, normalising the students’ experience and giving them a feeling of belonging and fitting into a group. The social network is monitored and regulated by expert facilitators. Moreover, a number of filters are embedded within the system to ensure that only students with mild to moderate difficulties are using it. Where applicable, those with more significant difficulties are referred to more appropriate services, such as their HEI student support mechanisms or mainstream helplines and help centres.

Students who want guided help can start using the system by completing the Questionnaire (symptoms-route). This interactive questionnaire follows a specific taxonomy to identify students’ psychological difficulties, focusing on anxiety and depression symptom. Additionally, symptoms of anxiety and depression have a high comorbidity. This was taken into account in the development of the initial Questionnaire, which differentiates between students who experience only anxiety symptoms, only depression symptoms, or a combination of both. The Questionnaire was designed to differentiate between the different types of presenting problem that were identified during development of the system as most prevalent in the target group (students) and for which there was clear evidence for the effect of this mode of supported self-help intervention.

The version of the Questionnaire in the described trial differentiates between three broad types of presenting problem, involving either predominant features of anxiety, or of depression, or mixed anxiety and depression features. The questionnaire statements have been adapted from established tools, including clinical questionnaires (Hospital Anxiety and Depression Scale [HADS] [26]; 7-item Generalised Anxiety Disorder Scale [GAD-7] [27]; Patient Health Questionnaire [PHQ-9] [28]) and a formal interview (Mini International Neuropsychiatric Interview [MINI] [29]). The HADS, GAD-7, and MINI informed the choice of anxiety questions. The HADS, PHQ-9, and MINI informed the choice of depression questions. iConcipio undertook extensive pilot testing (*n* = 491) that showed these questionnaire items to be acceptable and to effectively provide initial filtering of presenting problems ([name], personal communication). However, the Questionnaire is designed in such a way that it is expandable. Future launches of the system may include more questions and thus may cover a wider array of psychological difficulties. Upon completion of the Questionnaire, a package with techniques is suggested based on the best-fit intervention tailored to students’ identified needs.

An alternative route that can be followed by students is via the Library (techniques-route). Here, students can freely browse all the available psychological and educational techniques and create a personalised package to help them improve in the areas of personal effectiveness on which they choose to focus. Both routes lead to a personal space called ‘My Place’, where students will find their package of techniques, either the package assembled for them as determined by their ‘Questionnaire’ answers or the package that they have assembled themselves in the ‘Library’.

The psychological techniques are derived from CBT. There is strong evidence supporting the effectiveness of CBT in addressing a range of emotional difficulties and associated behaviours [30–33]. Techniques considered by the expert clinical team to most likely be acceptable, feasible, and effective in the target HE population were selected for inclusion in this intervention. The educational techniques consist of the most up-to-date practical skills, extensively tested and shown to improve students’ performance [34]. They aim to help students focus their efforts better and develop successful study skills and strategies.

The techniques are presented in the form of animated videos which demonstrate evidence-based psychological and/or study skill techniques. Videos are a pioneering media for communicating evidence-based techniques to non-expert audiences, as research shows that multimedia aids learning by engaging both verbal and visual information-processing channels [35, 36].

The system has a ‘bottom-up’ design, following a symptoms- and a techniques-driven approach, to avoid the potential stigma that may be associated with applying labels to difficulties. It aims to achieve more effective and immediate results by focusing on how to ‘cope’ better with the student’s current challenges. The language, visual appearance, and feel of the system are also chosen carefully to address its target group. Overall, this online intervention is based on current scientific knowledge and best practice, and provides a mosaic comprising implicit (e.g. nudge theory, [37]) and explicit (e.g. relaxation) state-of-the-art psychological and educational strategies (e.g. how to prepare for exams).

### Development

The development of MePlusMe has followed the Medical Research Council (MRC) guidelines for developing complex interventions [38]. The system has been developed in three stages, in collaboration with both students and HE providers. Initially, we conducted two market research projects. The first targeted counsellors and psychologists working in HEI SSS, using a semi-structured interview to collect information regarding the operation of existing services, and their common practices, needs, and challenges. The second project was conducted with HE students via an online survey, which will be detailed in a future publication ([name], [name], [name], [name], & [name]: Survey to inform the development of an online support system for higher education students: a brief report, sumitted). This research sheds light on the most common difficulties that students face at universities, their opinions of online support systems, and what features they believe make such systems useful.

Recently, a proof of concept study was completed with the participation of five UK HEIs (King’s College London, University of Edinburgh, University of Roehampton, Bournemouth University, and University of Warwick; *n* = 873 students) to ensure that the development of MePlusMe is acceptable and reflects end-users’ needs [[name], [name], [name], [name], [name], & [name]: Elearning support system for HE students with psychological and study skill difficulties: proof of concept study,” submitted]. During this study, uncertainties that were identified in the development of the system were examined, and feedback regarding the system’s acceptability and feasibility was obtained. Encouragingly, preliminary data showed that students like and need such a system.

In addition, an in-depth discussion with executives from HEIs took place following testing to gather their thoughts and opinions. This feedback alongside findings from the proof of concept study allowed refinement of the initial design. As an example, wording and graphics were altered to better appeal to an older student group, as well as younger students.

Moreover, the system is being continually developed in collaboration with two advisory boards. Firstly, the universities’ advisory board (UAB) ensures that MePlusMe addresses the requirements of HEIs services, as well as student needs. Secondly, iConcipio’s research and clinical team, consisting of senior academic and clinical psychologists from various HEIs and NHS hospitals, ensures that MePlusMe adheres to the best psychological practice, and that all research projects follow relevant guidelines.

### Aims of study

Following the activities outlined above, a full-scale feasibility study is now warranted. The study will commence in spring 2016 and recruitment of HEIs started in spring 2014. The study will evaluate the feasibility, acceptability, and potential effects of MePlusMe. It will specifically evaluate potential effects on students’ mood (symptoms of anxiety and depression), mental wellbeing, study skills, and everyday functioning, and their engagement and satisfaction with the system. This paper describes the protocol for the feasibility study. This is a crucial step, as its intended outcomes will inform a randomised controlled trial (RCT), leading to a wide-scale incorporation of the system within HEI SSS.

## Methods/design

### Setting and participants

Two UK HEIs that initially participated in our preliminary audit work (Bournemouth University and University of Warwick) will participate in the present study and will be given online access to MePlusMe.

All students enrolled at these HEIs will be eligible to be screened for inclusion. Any student with self-reported mild to moderate psychological and/or academic-related difficulties can participate in the study. Students with more significant difficulties will be excluded via a screening process within the system. All students will be presented with screening statements, including items on engagement in risky behaviours such as self-harm, substance abuse, and physical harm to others, as well as unusual sensory experiences or beliefs. Those who feel that any of the statements apply to them will be discouraged from proceeding to use the system, and will be directed to more appropriate sources of support for their difficulties.

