### Recruitment and consent

The participating HEIs will receive support from iConcipio to promote the study to their enrolled students via their usual communicating channels (social media, website, leaflets, and circular emails). Moreover, if the HEIs agree, SSS will be able to offer this system to students who are currently on their waiting list.

Students who are willing to participate in the study will log-in to the system and will be authenticated using university-provided credentials via single sign-on (SSO) services (e.g. Shibboleth, OAuth, LDAP lookup).^2^ They will then be directed to the information sheet. If they decide to proceed, they will access a screen listing risk statements (e.g. self-harm, substance abuse, physical harm to others, unusual sensory experiences or beliefs). At this stage, the students will not be asked to declare whether they identify with any of the statements, but they will be prompted to select either (i) the ‘proceed’ button if none of the statements applies to them or (ii) the ‘next’ button in case they need further guidance, which will lead them to a screen referring them to more appropriate services, such as their HEI student support mechanisms or mainstream helplines and help centres. If eligible (i.e. if they choose the ‘proceed’ button), the students will have access to a consent form, which they will need to sign in order to be able to register their details and use the system.

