### Intervention

Following screening, students will decide whether they want to access the Library, directly choosing the techniques they are interested in or whether they want guided help, entering the Questionnaire route to identify their difficulties. Should they choose the Questionnaire route, the students will be presented with the initial screen of the system which poses the question ‘What is your hotspot today?’ allowing each student to come into the questionnaire with whatever they think the presenting problem is. The three entry points are (i) ‘It’s how I am feeling inside’, addressing psychological difficulties, (ii) ‘It’s my studies’, addressing study skills problems, and (iii) ‘It’s outside pressures’. However, the questionnaire is designed in such a way that no matter which entry point the student chooses, they will always be directed to the other points at the end of each section.

Once they choose the techniques they are interested in from the Library or upon completion of the Questionnaire, the student will be asked to rate how much their difficulties are currently affecting their life. They will then have the opportunity to name their package of techniques so that they can later find it in their personal space. At this stage, they will also decide whether they want reminders to encourage them to return to watch the videos and practice the techniques. They will then be guided to My Place where they will have access to the package with the techniques. The student will be asked to rate again at different intervals (2, 4, and 8 weeks from baseline) how much their difficulties are affecting their life after practising these techniques, and their responses will result in a graph indicating their progress over time as a self-monitoring tool. If the students give two consecutive low ratings, they will be prompted by email with information on where to seek further support. Moreover, it is stated in the description of some techniques (e.g. the two psychoeducation techniques of understanding stress and understanding low mood) that if symptoms persist for more than 2 weeks, then students should seek support elsewhere (specific referrals are again provided). Students can make notes of their thoughts regarding the techniques and their experience of them, and are given the option either to keep their thoughts private or to share them within the system’s built-in social network.

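### The article says screening keeps out students with more than moderate difficulties, but the entry step it describes is a self-attested risk screen that does not check symptom severity

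*Protocol article*

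**What the plan says.** Two statements in the protocol article describe the population that screening will deliver. Under MePlusMe, filters are embedded "to ensure that only students with mild to moderate difficulties are using it". Under Setting and participants, "Students with more significant difficulties will be excluded via a screening process within the system". The same section gives the inclusion rule: "Any student with self-reported mild to moderate psychological and/or academic-related difficulties can participate in the study".

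The mechanism follows in two places. Setting and participants says all students see screening statements. The examples are self-harm, substance abuse, harm to others, and unusual sensory experiences or beliefs. It continues: "Those who feel that any of the statements apply to them will be discouraged from proceeding to use the system". Recruitment and consent adds that "At this stage, the students will not be asked to declare whether they identify with any of the statements". They press proceed if no statement applies, or next if they need guidance, which leads to a referral screen. Then: "If eligible (i.e. if they choose the ‘proceed’ button), the students will have access to a consent form".

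**The concern.** The two claims promise a property of the sample, namely that nobody above the moderate range is in it. The screen as described concerns risk behaviours and unusual experiences. These are not the same as severity of depression or anxiety, which is what the study measures.

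If the claims are taken at face value, the exploratory pre-post changes will be read as describing mild to moderate students, the group for whom the Discussion says the system is meant. If severe students have entered, that label is wrong, and nothing in the stated reporting would necessarily show it. There is also a care aspect. A student who scores in the severe range at baseline has been told, in effect, that the system suits them.

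**Working it through.** No figure in the plan depends on this point, so the check sets the claim beside each step in the article that could enforce it.

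| Step (section) | What it does | Does it stop a student with severe symptoms and no listed risk? |
|---|---|---|
| Self-reported mild to moderate criterion (Setting and participants) | States who may take part | Not on the text: no described step asks for a severity rating before entry |
| Risk statements (Setting and participants; Recruitment and consent) | Diverts those who recognise a listed risk and press next | No: this student would correctly press proceed |
| Questionnaire (MePlusMe; Intervention) | "differentiates between three broad types of presenting problem, involving either predominant features of anxiety, or of depression, or mixed anxiety and depression features" | No: it sorts by type of problem, and the Library route bypasses it |
| PHQ-9 and GAD-7 (Mood and wellbeing; Assessments) | Completed after consent as outcome measures | No: no upper limit is set |
| Rating of impact on life (Intervention) | "If the students give two consecutive low ratings, they will be prompted by email with information on where to seek further support" | No: it signposts and removes no one |

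Two consecutive ratings cannot exist before the second rating occasion. Ratings are taken at the start and at 2, 4 and 8 weeks. The email can therefore come no earlier than week 2 if the starting rating counts, or week 4 if it does not. A severe baseline PHQ-9 or GAD-7 score triggers nothing in the article.

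The row that decides the matter is the second. The gap does not depend on students answering dishonestly or ignoring advice. Full compliance with the named statements still admits the student in question.

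**What the planned data could show.** The article gives no share of severe students, so the share cannot be predicted, but the baseline scores would measure it. With n = 242 entrants (Sample size):

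- No severe scores: one-sided 95% upper limit = 1 − 0.05^(1/242) = 1.2%.
- 12 severe: 12/242 = 5.0%, exact (Clopper-Pearson) 95% interval 2.6% to 8.5%.
- 24 severe: 24/242 = 9.9%, exact 95% interval 6.5% to 14.4%.

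The counts 12 and 24 are illustrations and not forecasts. They show that a table from 242 entrants is precise enough either to support the mild to moderate label or to show that it needs qualifying.

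**The case against.** The strongest reply is that this is exclusion by self-report and that the article says so. The criterion is worded as self-reported, the proceed button is for students to whom no statement applies, and the next button leads away from consent. All of that stands. A reader might infer that the gate is mere advice and that anyone may walk in. The text does not support that reading, because choosing to proceed is a conditional self-attestation and those who select themselves out are diverted. What remains is that the attestation concerns listed risks and not severity, while the two claims say more than self-report can deliver.

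A second reply is that the phrase about more significant difficulties may mean the listed risks and nothing else. That would reconcile the sentences within Setting and participants. It does not reconcile the claim under MePlusMe, which is about admitting only mild to moderate users.

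A third is that an article condenses. The statement lists are introduced as examples, the filters are mentioned without being itemised, and Figure 1 cannot be seen. This limits the point to the steps described: it would be wrong to say that the study has no severity check at all. It does not remove the point, since the article describes entry down to the button labels and the mismatch lies within that description.

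A fourth is that the study is a feasibility study and its pre-post analyses are exploratory. This is correct, and it is why the issue is rated minor.

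**Conclusion.** The point holds in a limited form. The article claims a population restriction that its described entry procedure does not provide: on those steps a student with severe depression or anxiety and no listed risk can properly enter. This assumes that no undescribed filter or element of Figure 1 screens on severity.

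The consequence is confined to the population label on the exploratory pre-post results and to the signposting of severe students. Recruitment, retention and acceptability findings are unaffected. The SD taken without any severity restriction remains the right planning input if the future RCT uses the same gate.

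A reader might go further and infer that severe students will be present in numbers that bias the estimated change. The article does not support that. Support services may offer the system to students on their waiting lists if the institution agrees, which makes such entry plausible, but no share is given, and neither the size nor the direction of any effect can be derived. Nor is there a planned caseness analysis to be distorted: caseness appears only in the sample size calculation, not under Data analysis.

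**What to change.** 1. Reword the claims under MePlusMe and under Setting and participants. Say that entry is by self-selection after a risk-statement screen and that severity is not verified. If an undescribed filter does screen on severity, describe it instead.
2. Tabulate baseline PHQ-9 and GAD-7 by severity band, for all entrants and for completers, with the bands named in advance. Describe the exploratory pre-post results as applying to mild to moderate students only if this table supports it. Set no lower limit, because academic difficulties alone qualify for entry.
3. Send the existing signposting email when a baseline score falls in the severe range, without waiting for two low ratings. The clinical team should set the threshold.

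A re-estimate of change that leaves out students above the moderate range is optional at most. Selecting on the baseline score brings in regression to the mean and narrows the baseline SD, so it should not replace the unrestricted estimate.

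The cost is two reworded sentences, one table from scores already collected, and one added trigger for an email that already exists. No new data and no change in sample size are needed.
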